### **6.8.2. « English learning » intervention**

The intervention in the foreign language learning group (English) will be carried out by teachers from the Carré International, a department at the University of Caen dedicated to language learning and experience with the older people. This intervention will consist of English exercises aimed at reinforcing the skills of each participant in terms of written and oral comprehension and expression. A placement test will be offered during the first session to allow a precise evaluation of the initial level of each participant. The first session will also be devoted to the creation of a group spirit (introduction of each participant, commitment to participate in the sessions over the 18 months, rules of confidentiality, etc.).

Then the basics of English will be worked on (name, age, nationality, place of living, lifestyle, tastes, etc).

The other sessions will be a mix of activities that will allow the student to work on oral comprehension and expression, the acquisition of new vocabulary and new grammatical structures. A large part of the course will be devoted to reviewing the concepts covered in the previous courses.

Existing manuals will be used; these are methods that have been published and used in numerous training courses, particularly at the Carré International for several years.

Participants' progress will be evaluated using methods routinely used at the Carré International, including a training follow-up document and personalized or group assistance as needed.

The days and half-days will include similar exercises as well as games and artistic workshops where the emphasis will be on exchanges in English. A day on the Channel Island of Jersey will be organized where participants will have a mission to accomplish with informations to obtain on different places, objects to obtain (leaflets, ...) and objects to buy. The corresponding language needs will have been worked on beforehand.

Starting with the second wave, the foreign language learning group will be divided into 2 subgroups in order to respect the logistical constraints on group size. The allocation in each of the two English groups will be drawn at random via the eCRF randomization module and adapted by the English teachers if necessary from the level assessed during the English test carried out during the diagnostic battery, to limit the heterogeneity of level within the same group.

## **6.9. Visit no.2 - Intermediate evaluation visit at 9 months**

Nine months after the start of the intervention, each participant (including the passive control group) will be seen for a first intermediate visit. For this visit, only a short neuropsychological and behavioural assessment will be performed.

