## **2.2. Secondary objectives**

### **2.2.1. Secondary objectives in relation to the interventions**

**OBJECTIVE 2:** To compare the effects of the two interventions (meditation and foreign language learning, for 18 months) with each other and with a passive control in non-meditating seniors, on behavioural and biological measurements (cognitive, psycho-affective, blood, sleep, and imaging), including measurements to assess potential deleterious effects as well as gender-specific effects (men/women);

**OBJECTIVE 2 bis:** To estimate the maintenance of the effect of the interventions (meditation and foreign language learning) in the long term (29 months after the end of the intervention) on cognition, psycho-emotional factors, sleep, and lifestyle (and imaging and blood markers if the budget allows).

**OBJECTIVE 2 ter:** To compare the long-term effects (29 months after the end of the intervention) of the 2 interventions (meditation and foreign language learning) with each other on cognition, psycho-emotional factors, sleep, and lifestyle (and imaging and blood markers if the budget allows).

**OBJECTIVE 3:** To estimate the effect of the interventions (meditation and foreign language learning, for 18 months) on the volunteers' entourage (i.e., their perception of the volunteers' changes, their interaction with the volunteer, and their willingness to help the volunteer), compared to a passive control.

**OBJECTIVE 3 bis:** To compare the long-term effects of the interventions (meditation and foreign language learning) on the volunteers' entourage (i.e., their perception of the volunteers'

changes, their interaction with the volunteer, and their willingness to help the volunteer) 29 months after the intervention ended.

**OBJECTIVE 3 ter:** To estimate the effect of the interventions (meditation and foreign language learning, for 18 months) (i.e. their acceptance of the intervention, their perception of the changes...).

**OBJECTIVE 3 quater:** To assess the consistency between participants' perceptions of the interventions and their effects and those of the meditation or English teachers (after the interventions have ended).

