- Anthropometric measurements (weight (kg), fat (%), fat mass (kg), lean mass (kg), hydration rate (kg), muscle mass (kg), bone mass (kg), impedance (Ohm), basal metabolic rate (kJ; kcal), visceral fat (level) and metabolic age (year), as well as BMI, Sarcopenic Index (SMI; kg/m^2) and Skeletal Muscle Mass (SMM; kg and %).
- Charlson and CIRS scores
- Impact on the participants' entourage (OBJECTIVE 3):
  - Scores from the questionnaires given to the participants' partners as listed in Tables 5 and 6 below.
  - Qualitative data from interviews with participants and teachers.
- Neural signature of meditative practices (OBJECTIVE 5):
  - Measurement of neural activity in each brain voxel in fMRI at rest, and during the rest-SOVT task, in a mindfulness meditation state versus a non-meditative state ;
  - Measurement of neural activity in each brain voxel in fMRI at rest, and during the rest-SOVT task, in a compassionate meditative state versus a non-meditative state.
- Measurement of the tolerance to the intervention (OBJECTIVE 2):
  - Occurrence of adverse events;
  - Anxiety measured by the State-Trait anxiety Inventory (STAI);
  - Depression as measured by the Geriatric Depression Scale (GDS);
  - Positive and negative emotions measured by the questionnaire PANAS-NOW;
  - Satisfaction and well-being measured by self-questionnaires.

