## **6.8. 18-month intervention**

As mentioned above (6.7. Visit 1 - Inclusion Visit), the inclusion of the non-expert senior participants will be conducted in three waves of participants (divided into three arms). The waves will be spaced approximately 6 months apart. Interventions will therefore also begin in three waves spaced approximately 6 months apart, and all intervention groups will consist of 14 participants.

Participants will be asked not to engage in the proposed activity in the arms to which they have not been assigned for the duration of the intervention. Participants assigned to the meditation group and the foreign language group will have a standardized intervention program following a well-defined plan described in a detailed manual (for the meditation intervention) or following a specific program (for the foreign language intervention) lasting 18 months. Both interventions will be delivered by experienced and motivated teachers. The formats of the interventions will be identical in terms of the volume and frequency of sessions, home practice, and group exchange periods. The number of teachers per class and their level of expertise in delivering these programs will be identical between the interventions.

Thus, for both types of intervention, participants will have:

- Group classes of 2 hours, once a week,
- Exercises to be done every day for at least 20 minutes,
- More intensive days and/or half-days of practice.

In each weekly group session, there will be a time for presentation, a time for sharing, and a time for practice; the first two sessions of each month will include an equal amount of these three aspects (3x40min), session 3 will include more sharing (30/60/30min), and session 4 more practice (30/30/60). For each intervention, participants will be provided with supports (manual and audio) for their practice. The alternation of supports (texts, images, audio, video) and activities (alone, in pairs, in groups) will contribute to maintain interest and motivation.

Participants will be strongly encouraged to participate in all of these activities over the course of the intervention (18 months). In addition, they will be given a questionnaire at the beginning of the intervention to assess their expectations of the intervention (Credibility/Expectancy questionnaire, Devilly et al., 2000).

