Monthly meetings will be organized between the scientific investigators and the teachers of the two interventions in order to ensure the best possible follow-up. In case of specific problems, the teachers in charge of the intervention will immediately contact the scientific investigators in order to keep them informed and to ensure optimal care and follow-up of the participants.

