## **6.10. Visit no.3 – Follow-up visit**

At the end of the 18-month intervention, the participants will be welcomed back at the Cyceron center for a preliminary medical interview during which the physician will verify the absence of contraindication to the MRI examination (claustrophobia, ferromagnetic material in the body) and to the PET scan (known hypersensitivity to Amyvid® and Glucotep®), will update the participants' medical

history and drug treatments, and will declare any adverse events that may have occurred during this period. From the medical data collected during this interview, the comorbidity index will be calculated again (Charlson et al., 2008) as well as the CIRS score (see detailed description in V4). Then, the participants will be asked to perform again all the examinations of the inclusion visit (V1), namely:

- 2 MRI sessions,
- 2 PET Scans,
- a blood sample (3), conditioning the realization of the PET imaging to the same criteria as in V1 (cf 6.6),
- a detailed neuropsychological and behavioural assessment (V3),
- an examination of wakefulness (spontaneous EEG and MMN) and sleep.

Because some blood biomarkers and cognitive tests are not sensitive to longitudinal changes, they will not be repeated at this 18-month follow-up visit. Moreover, two behavioural tests (Cyberball (Williams et al., 2000) and Empathic Distractor (Klimecki et al., submitted); respectively evaluating social exclusion and empathy mechanisms), based on a surprise effect, can only be performed once and will be offered to non-expert seniors during this visit. A qualitative interview will be conducted with an evaluator experienced in conducting this type of interview (other than the neuropsychologists and members of the investigating team, this experimenter will be familiar with the intervention group). The open-ended semi-structured interview will last between 30 and 60 min and will be designed to collect data on the experience of learning English and meditation during their participation in the Age-Well trial. The V3 blood sample and the V3 neuropsychological and behavioural assessment are detailed in Tables 8 and 5 respectively.

The evaluators of the various examinations will not be aware of the participants' group assignment, and they will be instructed not to share it, except for the qualitative interview.

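### Adverse events are compared between arms, but no event enquiry is described before 18 months and only the active arms have regular contact, so active-versus-passive event counts may be unevenly ascertained

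*Combined protocol and SAP*

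**What the plan says.** Protocol section 2.2.1 (Objective 2) compares the two interventions with each other and with passive control, "including measurements to assess potential deleterious effects". Section 5.2 lists "Occurrence of adverse events" first among the tolerance criteria for that objective, and both SAPs carry adverse events under safety and acceptance for Objective 2.

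At 9 months "each participant (including the passive control group) will be seen for a first intermediate visit", but section 6.9 limits its content: "For this visit, only a short neuropsychological and behavioural assessment will be performed". Section 10.1.4 lists only test scores as V2 data. At V3 (section 6.10) a physician updates medical history and treatments and "will declare any adverse events that may have occurred during this period".

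Between visits the arms differ. Section 6.8 gives both active arms "Group classes of 2 hours, once a week" for 18 months. Teachers and investigators meet monthly, and if specific problems arise "the teachers in charge of the intervention will immediately contact the scientific investigators". Participants in these arms also complete a daily tablet questionnaire that ends with a free comment. The passive arm has no equivalent.

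Section 8.3.1 requires investigators to record all adverse events after V1, and section 8.3.3.1 requires serious events to be reported from consent to the end of follow-up. Neither depends on arm. Neither gives an interval or method of enquiry for non-serious events.

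**The concern.** A duty to report events does not create equal awareness of them. A participant seen every week has many occasions to mention a minor event. A passive-arm participant has one described contact in the period, V2, and no event question is planned there. If awareness differs, recorded events differ even when true rates are equal, and the difference runs towards more apparent harm in the active arms.

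What is at stake is the count of non-serious events in meditation or English against passive control. The SAPs tabulate events by group, and readers will compare the columns whether or not a test is run. Nothing in the plan would separate events that came out through class contact from those elicited equally in every arm.

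**Working it through.** The plan gives no event rate, event power or capture figure, so there is no number to reproduce. The check has two parts.

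**1. Contacts through which an event could come to light, by arm**

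| Contact | Meditation | English | Passive | Protocol section |
|---|---|---|---|---|
| Weekly class, 18 months | yes | yes | no | 6.8 |
| Monthly teacher–investigator meetings; immediate contact for problems | yes | yes | no | 6.8 |
| Daily tablet questionnaire with comment field | yes | yes | no | 5.4, 6.8 |
| Preliminary interview with a teacher; psychotherapist follow-up once effects appear | yes | no | no | 8.3.6 |
| V2, no event question described | yes | yes | yes | 6.9, 10.1.4 |
| V3 physician interview, with event enquiry | yes | yes | yes | 6.10 |
| V3 qualitative interview on the intervention | yes | yes | no | 6.10, 10.1.5 |

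The only row that is an event enquiry is common to all arms. The rows that differ are contacts, and none is described as a means of recording adverse events. The asymmetry is therefore one of opportunity, and it separates active from passive far more than meditation from English.

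**2. Illustration of size (assumed inputs)**

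Inputs: n = 50 per arm (protocol Table 1). The true risk p of at least one non-serious event is equal in both arms; p = 20%, 40% or 60% is assumed. Capture c is assumed at 90% in an active arm and 90%, 80%, 70% or 50% in the passive arm.

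- Observed risk = p × c, so the apparent risk ratio is c(active) / c(passive): 0.90/0.80 = 1.125; 0.90/0.70 = 1.29; 0.90/0.50 = 1.80.
- Chance of a false finding of more harm = Φ[(d − 1.96 × SE0) / SE1], where d is the observed difference, SE0 its pooled and SE1 its unpooled standard error.

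For p = 40% and 90% versus 70% capture:
- observed risks are 0.36 and 0.28, so d = 0.08 and the mean is 0.32;
- SE0 = √(0.32 × 0.68 × 2/50) = 0.0933;
- SE1 = √[(0.36 × 0.64 + 0.28 × 0.72)/50] = 0.0930;
- (0.08 − 1.96 × 0.0933)/0.0930 = −1.11, and Φ(−1.11) ≈ 13%.

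Chance of a false finding of more harm (nominal 2.5% in this direction):

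| True risk | Passive capture 90% | 80% | 70% | 50% |
|---|---|---|---|---|
| 20% | 2.5% | 4.5% | 7.8% | 20.8% |
| 40% | 2.5% | 6.2% | 13.4% | 42.8% |
| 60% | 2.5% | 8.7% | 22.2% | 68.6% |

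The Lockdown annex gives 135 seniors included, about 45 per arm. The 40% row then becomes 5.9%, 12.5% and 39.2% for the three unequal cases. With equal capture there is no bias. The result depends entirely on the capture gap, which the documents do not quantify.

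**The case against.** Much of the opposing case is sound and limits the point.

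- A reader might infer that teachers or tablets record adverse events. The documents do not say so. The teacher route is for keeping investigators informed and ensuring follow-up, and the tablet comment concerns the intervention in general.
- A reader might infer that the passive arm is covered only by 18-month recall. The V3 interview covers the same period in every arm, investigators must report events in all arms throughout, and passive participants have a referent and attend V2. This stands, although the referent's described role is organising appointments and accompanying visits, not asking about health between them.
- A reader might expect meditation to look worst of all. Section 6.8 gives the two interventions identical formats. The preliminary interview in section 8.3.6 is preventive, and the psychotherapist follow-up begins after an effect has been noticed. The support for a meditation–English bias is thin.
- The other tolerance measures include the anxiety, depression and affect scales, scheduled at V1, V2 and V3 for all non-expert seniors (protocol Table 5). They do not share the problem.
- Both SAPs list event severity and relationship for description by group, with no event-specific test. The false-positive figures would apply only if the general rules for qualitative secondary criteria (protocol section 11.3.6) were used.

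What remains is that no common event enquiry is described before V3, that contact is unequal, and that nothing in the analysis guards against the consequence.

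**Conclusion.** The point holds as a risk, not as an established bias. Non-serious events may be ascertained more completely in the active arms, and the active-versus-passive comparison may therefore overstate harm from the interventions. On the assumptions above, the apparent risk ratio runs from 1.0 with equal capture to 1.8 when passive capture falls to 50%. The documents cannot place the trial within that range.

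It would be tempting to conclude that the tolerance result is uninterpretable in either direction. That does not follow. This mechanism inflates events in the active arms, so a finding of no excess would be conservative. Only an apparent excess over passive control would be hard to interpret. Meditation versus English, and the questionnaire measures of tolerance, are largely outside the point.

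**What to change.** - **Collection.** Add one identically worded adverse-event question for all three arms at V2 and V3. It should preferably be self-completed, because V2 evaluators are meant to be blind and a spoken answer could reveal the arm. Record the source of each event: scheduled question, teacher, tablet or spontaneous report.
- **SAP.** Base the primary active-versus-passive event comparison on events elicited at these common visits plus serious adverse events. Count an event as visit-elicited if the participant mentions it there, even when it is already on file. Show all events, including those that came through teachers or the tablet, separately by arm without a test.
- **Safety reporting** to the sponsor is unchanged.
- **If V2 and V3 are complete.** Section 10.5 has the data through V3 frozen for transfer after 31 December 2020, so this may be the position. In that case restrict the comparison to V3-interview events plus serious events where records allow, and report unequal contact as a limitation.

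The cost is one short question at visits already scheduled, one eCRF field and a few lines of SAP text. The downside is that fewer events enter the comparison, and harms reported only to teachers appear in the descriptive listing alone.

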### **Neuropsychological and behavioural assessment on V2**

Each participant will be welcomed at the Cyceron center by their referent or an investigating psychologist to perform a set of cognitive tests. The battery of tests proposed will be shorter than the one proposed during the inclusion visit (see Table 5 above). All the tests and questionnaires will be carried out during the intermediate evaluation visit (V2) in a single session of about 2 hours, during which breaks will be scheduled.

The evaluators will not know the participants' group of assignment, who will be instructed not to communicate it.

## **6.10. Visit no.3 – Follow-up visit**

At the end of the 18-month intervention, the participants will be welcomed back at the Cyceron center for a preliminary medical interview during which the physician will verify the absence of contraindication to the MRI examination (claustrophobia, ferromagnetic material in the body) and to the PET scan (known hypersensitivity to Amyvid® and Glucotep®), will update the participants' medical

history and drug treatments, and will declare any adverse events that may have occurred during this period. From the medical data collected during this interview, the comorbidity index will be calculated again (Charlson et al., 2008) as well as the CIRS score (see detailed description in V4). Then, the participants will be asked to perform again all the examinations of the inclusion visit (V1), namely:

- 2 MRI sessions,
- 2 PET Scans,
- a blood sample (3), conditioning the realization of the PET imaging to the same criteria as in V1 (cf 6.6),
- a detailed neuropsychological and behavioural assessment (V3),
- an examination of wakefulness (spontaneous EEG and MMN) and sleep.

Because some blood biomarkers and cognitive tests are not sensitive to longitudinal changes, they will not be repeated at this 18-month follow-up visit. Moreover, two behavioural tests (Cyberball (Williams et al., 2000) and Empathic Distractor (Klimecki et al., submitted); respectively evaluating social exclusion and empathy mechanisms), based on a surprise effect, can only be performed once and will be offered to non-expert seniors during this visit. A qualitative interview will be conducted with an evaluator experienced in conducting this type of interview (other than the neuropsychologists and members of the investigating team, this experimenter will be familiar with the intervention group). The open-ended semi-structured interview will last between 30 and 60 min and will be designed to collect data on the experience of learning English and meditation during their participation in the Age-Well trial. The V3 blood sample and the V3 neuropsychological and behavioural assessment are detailed in Tables 8 and 5 respectively.

The evaluators of the various examinations will not be aware of the participants' group assignment, and they will be instructed not to share it, except for the qualitative interview.

A qualitative interview of the meditation and English teachers will be conducted with an evaluator experienced in conducting this type of interview (other than the neuropsychologists and members of the investigative team). The open-ended semi-structured interview will last between 30 and 60 min and will be designed to collect data on the Age-Well participants' perceptions of English learning and meditation. The consistency between the participant's perception and the teacher's perception will then be assessed.

